## Methods

### Study Design

This is a randomized controlled feeding trial with four groups. After screening, eligible participants and their caregiver(s) will visit the Clinical & Translational Research Center (CTRC) at Children's Hospital Colorado (CHCO) to complete the baseline visit (Figure 1) at 5 months of age. After obtaining informed consent, participants will be assigned and randomized to one of the four study diets: (1) a meat-protein-predominant diet group (Meat); (2) a dairy-protein-predominant diet group (Dairy); (3) a plant-protein-predominant diet group (Plant); or (4) a reference group without intervention (Reference).

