### Participants

Participants are being recruited in the metro Denver area from households with 3–4 month-old infants via direct mailing by Colorado Department of Public Health & Environment (CDPHE) which has access to the birth registry. Up to 300 infants will be recruited (75/group) to have at least 240 completers (60/group), based on a conservative estimate of 20% attrition.

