### Power Calculation and Sample Size Justification

We hypothesize that both the gut microbiota and infant growth trajectories are dependent on types of protein-rich foods consumed. We will recruit up to 75 infants/arm and use a conservative 20% attrition which results in 60/group (total completers *n* = 240). Sample size and power justification are from the longitudinal models with feeding group as the predictor and either gut microbiota (i.e., diversity and *Ruminococcus* abundance) and growth (i.e., linear growth parameter LAZ, overweight parameter WLZ and growth velocity using the WHO 0–24 months standards) as the outcomes. We completed power simulations (1,000 replicates) using a linear mixed-effects model (LME) with random effects by subject. For the simulations, we used parameter estimates (e.g., fixed and random effects) from our randomized pilot study on the gut microbiota and infant growth trajectories after receiving meat- or dairy-based complementary diet (30). We simulated a variety of scenarios assuming that Plant had microbiota and growth outcomes that were either worse than Dairy, between Dairy and Meat, or the same as Meat. *To be conservative, we estimated power after increasing the within-group variability by 50%*. The power is above 80% in all simulated scenarios (80–90%) where the effect size was simulated to be at least 50% of that observed in our pilot study (30). The power of most simulation scenarios was below 80% when the effect size was 25% of that observed in the pilot study (30).

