### Statistical Approach

Aim 1: Using ANOVA for continuous variables and chi-squared test for categorical variables, we will assess whether matching and randomness held by testing whether potential confounders (e.g., feeding mode, maternal height, maternal BMI, education, sex, race/ethnicity, and smoking during pregnancy) differ between groups. Variables with a *p* < 0.05 and those that have a strong association with the outcome of interest are included in future models. To model the relationship between diet, time, and diet by time interaction and LAZ and WLZ, we use LME model with random effects by subject. This structure explicitly models multiple time points per infant and can adjust for changes of cofounders during the intervention (e.g., a participant changed from breastfeeding to formula feeding at 9 months). Given a significant diet by time interaction, we will test pairwise differences in growth trajectories using Tukey's multiple comparisons.

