Aim 3: We use LME on growth Z scores and the microbiota over time with random effects by subject, and include group as a covariate. We also complete secondary analyses stratified by group to identify relationships between Z scores and microbiota that differ by group. We will use microbiota diversity measures and relative abundances of individual taxa and genes/pathways to model diversity and composition of the microbiota. We also include necessary confounders, e.g., change from breastfeeding to formula. To evaluate whether taxonomic and/or functional features of the microbiota mediate the relationship between diet and growth, we use a method and R package called MedTest (43). As in classic mediation analysis, MedTest evaluates three models (44). In reference to Figure 2, the first model estimates the direct path between protein-rich foods and the gut microbiota and implements as part of Aim 1 using MiRKAT. The second model estimates the path between protein-rich foods and infant growth and will be implemented using a standard linear model in R. The third model estimates the path between protein-rich foods and growth controlling for the path between gut microbiota and growth and will be implemented using MiRKAT. Using these three models, MedTest tests for significances of the mediation effect of the gut microbiota. Since it is unknown which microbiota features may mediate the relationship, MedTest implements multiple microbiota distances: unweighted (45), weighted (46), and generalized UniFrac (47) as well as Jaccard and Bray-Curtis distances. To ensure a well-controlled type-I error rate, MedTest uses a modified permutation procedure to arrive at an omnibus test over all distances.

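### Aim 3 looks for microbiota–growth relationships that differ by diet through separate within-group analyses, and no stated analysis tests whether the slope differs between groups

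*Protocol article*

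**What the plan says.** All references are to the protocol article.

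- **Design.** Study Design: "This is a randomized controlled feeding trial with four groups". Participants: "Up to 300 infants will be recruited (75/group) to have at least 240 completers (60/group), based on a conservative estimate of 20% attrition".
- **Main Aim 3 model** (Statistical Approach, Aim 3): "We use LME on growth Z scores and the microbiota over time with random effects by subject, and include group as a covariate".
- **Search for diet-specific relationships** (same paragraph): "We also complete secondary analyses stratified by group to identify relationships between Z scores and microbiota that differ by group".
- **Features examined** (same paragraph): "We will use microbiota diversity measures and relative abundances of individual taxa and genes/pathways to model diversity and composition of the microbiota".
- **Contrast with Aim 1** (Statistical Approach, Aim 1), where a difference between diets is first tested as an interaction: "Given a significant diet by time interaction, we will test pairwise differences in growth trajectories using Tukey's multiple comparisons".

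The Aim 3 paragraph also describes a mediation test with a permutation-based omnibus procedure over several distances. It mentions neither a microbiota-by-group term nor a formal comparison of the stratum estimates.

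**The concern.** The sentence on stratified analyses names both a method and an inferential goal, and the method does not deliver the goal. Whether the association differs by diet is a question about differences between slopes. Fitting each diet group on its own tests each slope against zero. A slope that is significant in one group and not in another is weak evidence that the two differ, because the gap can come from sampling error alone.

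The other Aim 3 analyses do not fill the gap. Group as a covariate shifts the mean Z score by diet and leaves the slope common. The mediation procedure asks whether the microbiota carries part of the diet effect on growth, not whether the microbiota–growth association varies by diet.

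At stake are statements such as a taxon being related to growth under one diet but not under another. These would bear on the mechanism that the Discussion puts forward, and they could be made on differences that no stated analysis has tested.

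**Working it through.** **1. The plan's own figure.** 75 per group × (1 − 0.20) = 60 completers per group, and 4 × 60 = 240. This reproduces the stated numbers. The article gives no power or effect size for the Aim 3 stratified analysis. Its 80–90% simulated power is for models with feeding group as the predictor; it does not carry over to Aim 3 and cannot be re-run, because the pilot parameters are not given.

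**2. Inputs.** From the article: 4 groups, 60 completers each. Assumed: two-sided 0.05 within each group; strata compared by which are significant; the same true association in every group; independent groups.

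**3. Formula.** With within-group power *p*, the chance that one to three of the four groups are significant is

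P(discordant) = 1 − *p*⁴ − (1 − *p*)⁴.

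| Within-group power *p* | Calculation | P(discordant) |
|---|---|---|
| 5% (no association) | 1 − 0.00001 − 0.8145 | 18.5% |
| 10% or 90% | 1 − 0.0001 − 0.6561 | 34% |
| 20% or 80% | 1 − 0.0016 − 0.4096 | 59% |
| 30% or 70% | 1 − 0.0081 − 0.2401 | 75% |
| 50% | 1 − 0.0625 − 0.0625 | 87.5% |
| 95% | same as 5%, by symmetry | 18.5% |
| 99% | 1 − 0.9606 − 0.0000 | 4% |

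Setting the formula equal to 0.5 gives *p* = 0.159 and 0.841. Discordance is therefore more likely than not only when within-group power lies between about 16% and 84%.

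**4. Simulation at the planned size.** 10,000 replicates of 4 × 60 infants, one value per infant, with a common correlation *r* in all groups. The comparison is a joint group-by-microbiota F test on 4 − 1 = 3 numerator and 240 − 8 = 232 denominator degrees of freedom, at 5%.

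| Common *r* | Discordant significance | Interaction test rejects |
|---|---|---|
| 0 | 18.5% | 5.0% |
| 0.10 | 39% | 5.3% |
| 0.15 | 61% | 5.1% |
| 0.20 | 80% | 4.8% |
| 0.25 | 88% | 5.0% |
| 0.30 | 80% | 5.3% |
| 0.35 | 60% | 5.0% |
| 0.40 | 35% | 5.2% |
| 0.50 | 5% | 5.0% |
| 0.60 | 0.2% | 4.9% |

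No true difference exists in any row, so both columns are false-positive rates for a diet-specific association. The interaction test stays at 4.8–5.3% throughout. The discordance rate depends on the strength of the common association. Repeated monthly measures would raise within-group power and move the range of *r* over which discordance is common.

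**The case against.** **The article never says that the strata will be compared by p-values.** This is correct. Stratified models also give slopes and intervals, which could be compared directly or by a heterogeneity test, and a condensed article may leave that step to an analysis plan that is not shown. The percentages above therefore depend on an assumption about how the strata are read. What remains is that the article does state a method for this purpose, and that separate fits alone do not test a difference. It also found room to specify an interaction for Aim 1.

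**A reader might infer that the approach will usually show a difference where none exists.** The documents do not support that. Even when strata are read by significance, the per-feature rate is 18.5% with no association and falls to about 5% or less once the common correlation reaches 0.50. Many of the features screened may have little or no association with growth. With no association anywhere, 10 independent features would give at least one discordant pattern with probability 1 − 0.8145¹⁰ = 87%. That is a multiplicity effect, separate from the fault in the stratified method.

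**The consequence is limited.** This stands. The analysis is labelled secondary, and none of the stated hypotheses is that the association differs by diet. A reader might infer that the trial's main conclusions are at risk, but the Aim 1 diet comparisons and the mediation test do not use the stratified fits.

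**An interaction model is not free of drawbacks.** This also stands. With a single added term it imposes common confounder effects and variance components across diets, which separate fits do not, and it can miss modest real differences.

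**Conclusion.** The point holds in a limited form. As written, Aim 3 seeks diet-specific microbiota–growth relationships by stratification, its main model has group only as a covariate, and no stated analysis tests whether the slope differs by diet. This part needs no assumption beyond the plain reading of the two sentences.

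The size is conditional. If strata are read by significance at two-sided 0.05, the false impression of a diet-specific association arises per feature with a probability that runs from 18.5% under no association to a peak of 87.5% at 50% within-group power, then falls back as power approaches 100%. Within-group power is not given and can only be shown as a range. The simulated rates also assume one value per infant. The change should be made, but it concerns a secondary analysis and leaves the primary diet comparisons untouched.

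**What to change.** 1. Add a microbiota × group interaction to the Aim 3 mixed model for each feature. Allow confounder effects to differ by group where there is reason to expect it.
2. Base any claim that an association differs by diet on the joint 3-df test of that interaction. Make pairwise slope comparisons only after it, in line with Aim 1.
3. State the false-discovery control applied to these tests across diversity measures, taxa and genes or pathways. The article states none for the Aim 3 features, so it cannot simply be carried over.
4. Keep the stratified fits, but report the within-group slopes with confidence intervals as description only.

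**Cost.** One model term (three parameters), with no new data and no change to trial conduct. The price is power: with two groups of equal precision, the variance of a difference in slopes is twice that of one slope, so its standard error is √2 ≈ 1.4 times as large. At about 60 infants per group, modest real differences may be missed. A non-significant interaction should therefore be reported as inconclusive, not as evidence that the association is the same under all diets.

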**Figure 2 F2:**
[figure not shown]
Mediation analysis.

## Discussion

### Innovation and Significance

We focus on a critical developmental phase that has not been well-studied and propose a novel concept that during early complementary feeding, types of common protein-rich foods will differentially impact infant growth and risk of overweight and that gut microbiota will mediate this impact. To our knowledge, this is the first RCT that directly compared meat, dairy and plant consumptions on infant growth and gut microbiota. We also propose to use non-invasive body composition assessment with doubly labeled water, which also provides a reliable estimation of energy expenditure, a crucial component to assess the risk of overweight. Furthermore, we propose a plausible mechanism that protein-rich foods from different sources could impact infant growth trajectories by modulating the gut microbiota. Overall, this project is innovative because it is a substantively different concept and approach. It will greatly support implementing effective dietary interventions to prevent undesirable infant growth patterns and long-term negative health impact.

### Compliance Monitoring

Although we will use controlled feeding, we are aware that compliance with the dietary regime is a major challenge. Building on extensive experience, we will utilize the following strategies to optimize and monitor compliance: (1) A weekly multiple-choice log to record food intake based on the monthly recommendations (Table 1) as described in our pilot study (30). (2) Caregivers will be asked to return unconsumed foods/formula at the monthly home visit. (3) Weighed 3-day diet record will be collected at 5, 9, and 12 months; (4) Blood urea nitrogen (BUN), measured at 5 and 12 months is a crude marker of total protein intake, and values of BUN will reflect the total amount of protein consumed for comparisons between groups and over time. We also understand the study procedures may be burdensome to some caregivers. Our team has successfully conducted a number of infant trials with similar or more extensive procedures and low drop-out rate (30, 39, 48, 49). Our experienced team members are dedicated to fully support caregivers and will be available by phone/email and in person, and will make extra home visits if needed.

### Risks

The study protocol is expected to have minimal risk because there are no invasive procedures except the three blood draws at 5, 12, and 24 months of age, which are necessary to answer the research question. The 12-month blood draw will include analyses (Pb and Hb) routinely obtained for well-child surveillance; results will be provided to the primary care provider to avoid a second clinical blood draw. There is an unlikely risk of food allergies. During screening, the caregiver is asked if the infant has any food restrictions or allergies, including milk/dairy protein allergies (i.e., on a special formula). If the answer is yes, the infant is not eligible to participate. If the participant has no food restrictions or allergies, he/she is unlikely to be allergic to the complementary foods provided because most of the study foods are not considered highly allergenic foods. At the baseline visit, the study coordinator explains the potential risk of allergy development when starting complementary feeding and caregivers are given a list of common signs of food allergies. Food allergy is closely monitored by monthly health questionnaires. If repeated concerns are expressed, the participant will be removed from the study and advised to consult the primary care physician.

